## Abstract

**Background:**

Mild cognitive impairment (MCI) is a critical transitional stage in dementia related disorders. In that context, dorsolateral prefrontal cortex (DLPFC), and lateral parietal cortex (LPC) are subjected to neuropathological changes in MCI. Furthermore, alterations in parietal memory network (PMN) integrity and default mode network (DMN) also occur in MCI. Transcranial direct current stimulation (tDCS) is a promising neuroprotective tool that might interfere with cognitive decline in Alzheimer’s disease-MCI (aMCI) and Parkinson’s disease-MCI (PD-MCI) when applied to DLPFC or LPC separately.

**Methods:**

This is a randomized and controlled study evaluating the effectiveness of tDCS in 120 patients (60 aMCI and 60 PD-MCI). Firstly, all patients will be randomly (1:1) divided into two groups: DLPFC (30 aMCI; 30 PD-MCI) and LPC (30 aMCI, 30 PD-MCI) for tDCS stimulation. Secondly, they will classify randomly (2:1) real and sham groups for tDCS applied to once a day for 10 days over 2 weeks. The stimulation will be delivered with a 2-mA current frequency and will last 20 min. The primary outcome assessment for this study will be the change in score from baseline to the end of (14-days and 90 days follow-up) the tDCS application for the neurocognitive tests. Potential outcome parameters will be discussed in the light of current literature to contribute to the new area of personalized non-invasive brain stimulation research in neurodegenerative diseases at early stages. The results of this study are expected to shed light on the neural underpinnings and pro-cognitive outcomes of tDCS. Potential outcome parameters will be discussed in the light of current literature to contribute to the new area of personalized non-invasive brain stimulation research in neurodegenerative diseases at early stages.

## Background

Mild cognitive impairment (MCI) is used as a term to describe the period between cognitively healthy aging and cognitively dysfunctional aging. Technically, MCI is defined as 1–1.5 standard deviations beneath the normative data in neuro-assessment for the same age group, which is suggested to be sufficient for accurate clinical diagnosis (Albert et al., 2011; Petersen, 2004; Petersen et al., 2014). There are two different sub-groups of MCI, depending on the cognitive domain affected. Amnestic MCI (aMCI) refers to the impairment in cognition when the memory area is predominantly affected, while non-memory domains if affected are categorized as non-amnestic MCI. However, irrespective of the heterogeneous clinical course described above, MCI is a critical transitional stage in which early interventions can be applied to slow the cognitive deterioration. Thus, the recent framework (Diagnostic and Statistical Manual of Mental Disorders: DSM-5) suggested that MCI, as a transition phase, both accompanies the Alzheimer’s disease (AD) processes, and other various degenerative neurological disease processes (American Psychiatric Association, 2022; Carver et al., 2014).

As in AD, MCI can also be observed in the initial stages of Parkinson’s disease (PD), presenting in 18.9–38.2% of PD cases (PD-MCI) characterized by critical deficits in cognitive subdomains (Litvan et al., 2012). Furthermore, there is convincing evidence that PD-MCI is predictive of PD-Dementia (Litvan et al., 2011).

Specific cognitive deficits occurring in the prodromal stage in AD-MCI and PD-MCI are also associated with several biomarker changes during the progression to dementia, particularly including the amyloid beta burden and Lewy Body pathology (Aarsland et al., 2021; Besser et al., 2016). Furthermore, despite some disease-specific alterations, there is convincing evidence showing that Lewy Body pathology and neurofibrillary degeneration are common pathologies reported in both PD-MCI and AD-MCI participants (Besser et al., 2016), making a clear-cut differential diagnosis difficult when considering only the biomarker changes in the early phases of both disorders. The same is also true for brain network changes; for instance, several common cognitive networks, such as the lateral parietal cortex (LPC), dorsolateral prefrontal cortex (DLPFC), default mode network (DMN), and parietal memory network (PMN), are affected during neurodegenerative disease progressions (Buckner et al., 2005; Celone et al., 2006; Gratwicke et al., 2015; Sestieri et al., 2011), including both PD and AD.

Among them, DMN, with its well-known role in several memory functions (Kwon et al., 2023; Sestieri et al., 2011) also belongs to a network known as the PMN (Gilmore et al., 2015; Kwon et al., 2023). PMN is a recently defined network, functionally dissociated from the DMN, not only in particular recall tasks (coding, retrieval of recognition memory) but also in resting states during the aging process, indicating its critical role in age-related dementia disorders (Hu et al., 2019). This aligns with recent literature suggesting that functional and integrity alterations involving DMN, PMN, and the posterior control network (PCN) play a critical role in cognitive performance in AD and PD-MCI (Gilmore et al., 2015; Hu et al., 2019; Sestieri et al., 2011).

These findings together support that PMN alterations, in addition to DMN and LPC, may represent a powerful imaging biomarker, increasing the predictive value for the detection of impairments in cognition at the initial stages of AD and PD. Considering all this evidence, stimulating relevant brain structures, particularly the PMN, with transcranial direct current (tDCS) may serve as an impactful modulation technique for inducing pro-cognitive effects against neural impairment, as suggested for DMN in MCI patients (Hanoglu et al., 2023; Hunter et al., 2015). This approach will be advantageous against the conventional framework for research purposes in non-symptomatic degenerative phases associated with cognitive deficits.

## Hypothesis

The main objective of this study is to strengthen the evidence for clinical efficacy of tDCS in patients with mild cognitive impairment, while simultaneously embedding a mechanistic neuroimaging and electrophysiological perspective, and comparing the clinical effectiveness to determine if repeated stimulation over the parietal memory network or the DLPFC will yield measurable differences in improvements in cognitive performances compared with sham stimulation. Our secondary hypotheses aim to evaluate whether these cognitive improvements will be mediated by modulation of network-level integrity in the PMN and DMN, as will be assessed through resting-state functional MRI (fMRI) and EEG connectivity measures.

Regarding the rTMS, there have been considerable recent studies that analyzed the efficacy and safety of rTMS and tDCS in individuals with cognitive impairment and patients with Alzheimer’s Disease and MCI, and even in healthy individuals. For instance, several rTMS studies (Hanoglu et al., 2022, 2023) are showing promising results in AD, MCI, and PD (Jung et al., 2024; Zhang et al., 2022). A recent meta-analysis of 22 studies (1,074 patients) provides a good example of the beneficial effect of rTMS in AD and MCI, confirming the results by Hou et al. (2024). Also, a very recent work by Jung et al. showed that hippocampus and precuneuss- targeted repetitive transcranial magnetic stimulation (rTMS) increased functional connectivity and improved cognitive test scores in early AD patients (Jung et al., 2024).

Among the various non-invasive neuromodulation tools, tDCS works by stimulating the neurons via modulation of membrane polarity through increasing and reducing their excitability via anodal and cathodal stimulation, respectively (Angelakis et al., 2014; Bourdillon et al., 2019; Yamada and Sumiyoshi, 2021). In pathophysiological terms, tDCS application alters the signaling and transmission of various neurometabolites, which correlates with specific regional brain activity. tDCS is also used for the enhancement of cognition and emotional regulation (Hunter et al., 2015; Yamada and Sumiyoshi, 2021) associated with reversible reorganization of the altered whole-brain connectivity on both functional and structural levels. In light of the above, it appears reasonable to hypothesize that anodal tDCS stimulation of DLPFC and LPC may result in improved memory skills and executive functions in PD-MCI and AD-MCI patients, which may be associated with critical DMN, PMN and hippocampal connectivity changes. Within that context, several studies have suggested the pro-cognitive effects of tDCS in PD-MCI and AD-MCI patients (Angelakis et al., 2014; Brak et al., 2022; Ferrucci et al., 2008; Liu et al., 2021; Marceglia et al., 2016), a fact which has already been suggested in patients at dementia stage. For instance, a recent meta-analysis highlighted that anodal tDCS and 20 Hz TMS significantly improved cognitive function in AD by modulating neural activity (Andrade et al., 2024). Also, a notable example is a recent study that showed a significant improvement in age-related cognitive decline (Flöel, 2014).

Additionally, other studies have confirmed tDCS’s role in enhancing cognitive task performance, reducing pathological brain activity, and improving disturbed brain connectivity patterns in patients at the dementia stage (Boggio et al., 2009; Meinzer et al., 2015). The beneficial role of tDCS in AD has also been confirmed by a very recent study by LoBue et al. that high definition tDCS produced meaningful cognitive enhancements in a proportion of patients having AD with improvements maintained for at least 8 weeks in some when targeting the medial prefrontal cortex (LoBue et al., 2025). It is also worth mentioning that the beneficial effects of tDCS on cognitive function have also been demonstrated in healthy individuals. For example, a study on healthy adults showed improved visuospatial working memory performance after anodal tDCS (Jeon and Han, 2012).

Given that tDCS exhibits similar pro-cognitive effects in patients with dementia (Bystad et al., 2016; Rasmussen et al., 2021), it may be advantageous due to its properties, such as being user-friendly, relatively inexpensive, and well-tolerated compared to similar non-invasive brain stimulation devices like rTMS (Mehta et al., 2024; Vanneste et al., 2010). Furthermore, no serious side effects have been reported with tDCS, supporting its use in cognitive research on early dementia. Although recent evidence indicates a greater efficacy in combined interventions involving neuromodulation and cognitive therapy, this combinatory approach has some caveats, such as the standardization of the cognitive therapy, the quality and quantity of well-educated cognitive therapists as well as tDCS stimulation side and sessions (Horczak et al., 2023; Lau et al., 2024; Lawrence et al., 2018).

There are limited studies of tDCS and cognitive therapy (CT) applied in the early stages of dementia (de Sousa et al., 2020; Gonzalez et al., 2021; Inagawa et al., 2019; Lu et al., 2019; Martin et al., 2019; Rodella et al., 2022) compared to relatively rich literature on rTMS and AD studies. For instance, a recent meta-analysis suggested that tDCS combined with CT offers significant advantages in improving language function in MCI (Yang et al., 2024). However, a recent novel study conducted by Antonenko et al. showed that cognitive therapy sessions with concurrent tDCS application did not lead to a cognitive improvement in individuals with cognitive impairment leading again to the questioning of the effect of cognitive training in this population (Antonenko et al., 2024). This has also been suggested by a recent study, which shows only significant connectivity changes in the combination group without a significant behavioral effect (Šimko et al., 2024). Finally, very recent a systematic review and meta-analyses covering 3,828 studies revealed that there was no difference of the impact of tDCS and CT versus tDCS alone indicating even better outcomes in the tDCS alone arm (Prathum et al., 2025).

To conclude, several studies have suggested the pro-cognitive effects of tDCS in PD-MCI and AD-MCI patients (Angelakis et al., 2014; Brak et al., 2022; Ferrucci et al., 2008; Liu et al., 2021; Marceglia et al., 2016). However, methodologically, there is no head-to-head study comparing the effects of tDCS in both disorders simultaneously. Furthermore, these studies are limited to specific areas of application, which miss the beneficial effects of stimulating the novel PMN network. Additionally, despite strong design and powerful analysis methods, these trials included only a limited number of participants.

In light of the above gaps, the primary aim of the current study is to explore the modulatory effects of tDCS application over the DLPFC and LPC regions. The secondary aim is to evaluate the network and cognitive correlates of tDCS, with a focus on the PMN, DMN network, and hippocampal connectivity properties.

## Evaluation of the hypothesis

As briefly mentioned above, the primary endpoint of this study is the effect of anodal tDCS on cognitive improvement in patients with MCI, as measured by changes in performance on a standardized neurocognitive test battery. Composite *z*-scores will be derived for parietal memory network–related memory measures (primary composite outcome) and executive-function tasks (key secondary cognitive outcomes). Cognitive assessments will be performed at baseline, immediately after the intervention (Day 14), and at follow-up (Day 90).

The secondary endpoints are the neural correlates of stimulation-induced cognitive changes, assessed through multimodal neuroimaging and electrophysiological measures. Resting-state functional MRI will be used to evaluate alterations in structural and functional connectivity within the default mode network (DMN), parietal memory network (PMN), and hippocampal regions, alongside entropy measures (Shannon and permutation entropy). Quantitative Electroencephalogram (EEG) will be used to capture changes in electrophysiological activity, including power spectral density, coherence, and network connectivity indices. These secondary measures will provide connection insights into the network-level effects of tDCS and their relationship to cognitive outcomes.

### Study design

This multi-center, randomized, double-blind controlled trial (ClinicalTrials.gov Identifier: NCT05919485) aims to evaluate the efficacy of anodal tDCS applied over the DLPC and LPC in improving cognitive performance in patients with PD-MCI and AD-MCI (Figure 1). All participants will be informed of experimental goals of this study. Written informed consent will be obtained. This study protocol was approved by Istanbul Medipol University Ethics Committee (No:161/16.02.2023) and complied with ethical standards based on the Declaration of Helsinki.

**Figure 1 fig1:**
[figure not shown]
Study design and group allocation. Flowchart illustrating the study design for participants meeting inclusion criteria. Initial neurocognitive assessments, EEG, and fMRI were performed on 60 individuals with aMCI and 60 with PD-MCI. Participants were randomized in a 1:1 ratio to receive tDCS targeting either the DLPFC or the LPC. Within each stimulation arm, participants were further randomized in a 2:1 ratio to the Real or Sham tDCS condition, yielding 20 aMCI and 20 PD-MCI (real) versus 10 aMCI and 10 PD-MCI (sham). Created with BioRender.com.

### Participants

The randomly generated group assignment list will be produced by statisticians not involved in data collection, and participants with either amnestic MCI (*n* = 60) or PD-MCI (*n* = 60) will be assigned in a 1:1 ratio to either the DLPFC or the LPC group. As a second step, the device administrator will configure the device according to the assignment list based on participants’ registration numbers, which will be set to either sham or active mode via the administration menu. Finally, 30 PD-MCI and 30 AD-MCI patients will receive either real or sham stimulation in a 2:1 ratio (Figure 1). Since only the device administrator, who will not interact with the participants, is aware of the assignment list and the password needed to access the administration menu, other investigators and participants will remain blinded.

All participants will receive 2 mA tDCS in one session per day, administered over 10 days within 2 weeks, followed by a 90-day post-intervention assessment (Figure 2). For enrolment in the study, participants will be assessed using inclusion and exclusion criteria, accompanied by the Mini-Mental State Examination (MMSE), Montreal Cognitive Assessment (MoCA), and Clinical Dementia Rating (CDR) to evaluate dementia severity.

**Figure 2 fig2:**
[figure not shown]
Timeline of the tDCS intervention protocol. Assessments were conducted at three time points: baseline (Day 0, T0), post-intervention (Day 14, T1), and follow-up (Day 90, T2). Cognitive testing and electroencephalography (EEG) were performed at each time point, while functional magnetic resonance imaging (fMRI) was performed at baseline and follow-up. Participants received tDCS sessions five days per week between baseline and post-intervention. Created with BioRender.com.

### Inclusion criteria

Selection criteria are: (1) Literate and between 45 and 80 years of age; and (2) Score of 19–23 points for MMSE and <26 points for MoCA; (3) clinical diagnosis will be conducted by a skilled neurologist using DSM-V (Diagnostic Statistical Manual of Mental Disorders, fifth edition) criteria for mild neurocognitive disorder.

### Exclusion criteria

Exclusion criteria are as follows: (1) history of dementia or intellectual disability; (2) use of cognitive enhancers (donepezil, rivastigmine, galantamine, and memantine); (3) reversible medical conditions associated with potential cognitive impairment (e.g., history of vitamin B12 deficiency or hypothyroidism); (4) history of neuropsychiatric disorder such as cerebrovascular surgery, brain trauma, demyelinating diseases, epilepsy, bipolar disorder, major depressive disorder, schizophrenia, anxiety disorders, and substance abuse; (5) Having medical issues that prevent undergoing fMRI or for tDCS application; (6) Illiterate or education level less than primary school.

### Procedures

#### Assessment procedures

Neuropsychological testing will be conducted at baseline, after the intervention (at 14th day), and at follow-up (at 90th day). The test batteries listed below have already been used in a comparison study about PD-MCI vs. AD-MCI.

Attention: Digit Span Forward and Backward (Wechsler Memory Scale–Revised, WMS-R)Processing speed: Digit Symbol (Wechsler Adult Intelligence Scale–Revised, WAIS-R), Trail Making Test Part AExecutive function: Trail Making Test Part BEpisodic memory: Immediate and Delayed Logical Memory (WMS-R)Language: Animal fluency, Vegetable fluency, Boston Naming Test (BNT)Visuospatial ability: MMSE pentagon score (1 ¼ correct, 0 ¼ incorrect) and through clock-drawing (3 points), and cube copy (1 point) in MOCA.The Clinical Dementia Rating–Sum of Boxes (CDR-SB) will be completed at each visit. The CDR sum of boxes (CDR-SB) is a summary measure of scores for memory, orientation, judgment, community affairs, home and hobbies, and personal care, and ranges from 0 (no impairment) to 18 (greatest impairment).

#### Intervention procedures

The electrode will be located by placing the anode on the left DLPFC (F3), as positioned in the 10–20 international EEG system, and the cathodal electrode will be positioned over the contralateral supraorbital zone. In the LPC stimulation group, one electrode was positioned over P3 while the cathodal electrode was placed on the contralateral supraorbital zone.

The current density will be 0.06 mA/cm^2^ from each electrode with total density of 0.054/cm2 and will be delivered for 20 min a day for 10 days over 14 days.

For the sham protocol, stimulation will be delivered once with a very low current frequency, sufficient to cause slight tingling, and will last 15 s, with a total duration of 20 min. The number of sessions and days will be the same as the real group.

Electrode placement will be individualized using SimNIBS (Saturnino et al., 2019) software to optimize current flow targeting.

A safety strategy for tDCS will be applied throughout the whole procedure in the hospital by the same skilled investigator. Medical issues, including scalp malformation, inflammatory reaction, or other dermatological problems, will be examined by researchers during each visit.

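### The sham current is described as weaker than the 2 mA real current and conflicts with a statement that everyone receives 2 mA, which puts the participant blind for real versus sham at avoidable risk

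*Protocol article*

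**What the plan says.** Intervention procedures in the protocol article holds the only description of the sham: "stimulation will be delivered once with a very low current frequency, sufficient to cause slight tingling, and will last 15 s". The sham session also lasts 20 min in total, and on the schedule the section adds: "The number of sessions and days will be the same as the real group".

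For the real dose, the Methods part of the Abstract says: "The stimulation will be delivered with a 2-mA current frequency and will last 20 min". The Participants section gives a current without separating the arms: "All participants will receive 2 mA tDCS in one session per day".

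On blinding, Study design opens with "This multi-center, randomized, double-blind controlled trial". The Participants section explains how this is achieved. A device administrator, who does not interact with participants, holds the assignment list and the password. This person configures each device, "which will be set to either sham or active mode via the administration menu". The section concludes that "other investigators and participants will remain blinded".

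Under Hypothesis, the main objective asks whether stimulation at either site "will yield measurable differences in improvements in cognitive performances compared with sham stimulation".

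**The concern.** Blinding of participants in a sham-controlled stimulation trial needs two things. The allocation must be hidden, and the two conditions must feel enough alike that a patient cannot work out which one was given. The article deals with the first in some detail. On the second, the stated sham current is low, while the real current is 2 mA.

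At stake is the comparison on which the main objective rests. The primary endpoint (Evaluation of the hypothesis) is the effect of anodal tDCS on neurocognitive test performance. If patients can infer their arm from what they feel, expectation could contribute to the difference between real and sham. The model under Statistical analyses could not separate that contribution from an effect of stimulation, because both would follow the Group factor.

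**Working it through.** No sample size or power figure bears on this point, so there is none to reproduce. The check is a comparison of texts, followed by a count of what is exposed.

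**1. What the sham current is.** The Abstract and Intervention procedures both use the phrase current frequency. Direct current has no frequency to set, and the Abstract attaches the phrase to 2 mA, so it means intensity. Read the same way, the sham text sets an intensity well below 2 mA. It gives no value in mA, so the ratio to the real current cannot be computed.

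**2. What sham shares with real.** Intervention procedures matches three things: session length (20 min), number of sessions, and days. The current is not among them and is described as low. The phrase saying that sham is delivered once most likely means once at the start of each session.

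**3. Whether the short on-time is the defect.** It is not. The sham current runs for 15 s of 20 × 60 = 1,200 s, and 15 / 1,200 = 1.25% of the session. A brief opening followed by no current can be a sound sham. The question is the intensity during those 15 s.

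**4. The conflict.** Taken literally, the Participants section gives 2 mA to sham patients too. Intervention procedures gives them a very low current. Both cannot be right. The Participants sentence may be loose wording for the active dose, because the preceding paragraph sets devices to sham or active. It may also reflect a sham mode that opens briefly at 2 mA. The article does not settle which.

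**5. What the safeguards cover.** The assignment list, the password and the separate administrator conceal the allocation. None of them acts on sensation. The one sensory element is the tingling in the sham text, and it is tied to the low current, not to the sensation in the real arm.

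**6. Who is exposed.** Inputs: Figure 1 gives, at each target, 20 aMCI and 20 PD-MCI real, with 10 and 10 sham. The schedule is 10 sessions.
- Per diagnosis over two targets: 2 × 20 = 40 real, 2 × 10 = 20 sham.
- Both diagnoses: 2 × 40 = 80 real, 2 × 20 = 40 sham.
- Sham sessions: 40 × 10 = 400.

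**7. Where a bias would go.** Let expectation add b₁ to the real-minus-sham change at DLPFC and b₂ at LPC.
- Real versus sham, averaged over targets: bias = (b₁ + b₂) / 2.
- Group × Target × Time: bias = b₁ − b₂.
- Real DLPFC versus real LPC (20 v 20 per diagnosis): no sham patients enter, so the sham current cannot bias it.

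If b₁ = b₂ = b, the first bias is b and the second is 0. The equality is an assumption; nothing in the article establishes it. The article also gives no basis for the size of b, so none is put in.

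**The case against.** The strongest reply is that the real onset is never described. The article gives the real dose (2 mA, 20 min, a current density) but no ramp, opening current or expected sensation. Setting the sham opening against the real arm's overall dose is therefore partly inference. This stands. A reader might infer that sham fails to reproduce the start of real stimulation, or that patients will be unblinded. The article does not support either statement.

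Three further points also carry weight:
- The sham is set by its effect, enough to cause tingling, and its session length and schedule match real. Some masking is intended.
- The design is parallel. Each patient feels one condition and cannot compare the two, so a sham patient would have to infer the arm from a faint sensation alone. This lowers the risk. It does not remove it, because participants are told the experimental goals (Study design) and attend 10 sessions.
- The prose is loose, and the Participants sentence could mean a brief 2 mA sham. If so, the device may already do what is wanted.

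One reply does not succeed: that ramp and hold times are details an article may leave to the full protocol. Their absence is not the point. The article states a sham intensity, that intensity is lower than real, and another section contradicts it.

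**Conclusion.** The point holds in a limited form. The article conflicts with itself on the current that sham patients receive, and its only specific sham text describes a weaker stimulus than the 2 mA real one. The participant blind for real versus sham is therefore at avoidable risk. It is not shown to fail.

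The exposure is the whole sham arm and the comparison that the main objective names. The counts in the working measure that exposure, not harm; the size of any bias is unknown. A reader might also infer that the planned Group × Target × Time contrast is safe. That is so only if any expectation effect is equal at both targets.

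The conclusion rests on reading current frequency as intensity, which the Abstract's use of the phrase supports. It should be corrected because it touches the central comparison and the remedy is cheap. Confidence is moderate, because the device's actual sham setting is not stated.

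**What to change.** 1. Confirm what current the device's sham mode delivers at the start of a session.
2. In Intervention procedures, specify the sham along these lines: the device ramps to the same current as in real sessions (2 mA) at the same rate, holds briefly and ramps off; electrodes stay in place without current until 20 min. The sponsor sets the ramp and hold times. Replace current frequency with current intensity.
3. In Participants, limit 2 mA for 20 min to the real arms, and say that sham patients follow the same schedule with the sham defined under Intervention procedures.

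If the device's sham mode already opens like real stimulation, only the wording changes. If it does not, the setting changes, and the sham version must be recorded for every patient already treated. The sham arm would then contain two versions, which is the main drawback. No visits or patients are added.
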